### Secondary outcomes

#### Cardiac autonomic modulation

Linear analysis – time domain (heart rate variability) and frequency domain (absolute and normalized spectral component of low- and high-band frequencies to evaluate sympathetic and parasympathetic modulation, respectively, and autonomic balance) [44]Nonlinear analysis – symbolic analysis using four symbolic families (0 V%, 1 V%, 2LV% and 2ULV%) to evaluate sympathetic and parasympathetic modulation and Shannon entropy [45–47]

#### Vasomotor autonomic modulation

Linear analysis – time domain (BP variability) and frequency domain: low absolute component frequency (sympathetic vasomotor index) [48]

#### Spontaneous baroreflex sensitivity

Linear analysis – frequency domain method: alpha index by cross-analysis between SBP spectral power and RR interval spectral power (spontaneous baroreflex control of heart rate) [49, 50]

#### Forearm blood flow and peripheral vascular resistance

Evaluation of blood flow via assessment of the vascular tissue volume change in the forearm. The rate of the volume change is proportional to the rate of arterial inflow [43]. Forearm vascular resistance will be calculated as the ratio of mean BP and forearm blood flow

## Statistical analysis

### Power and sample size

Sample size was calculated using ABPM as the main outcome. Considering the high variance in the results with resistant hypertensive patients [29, 30] and the meta-analysis results of Fagard [28] with hypertensive patients, BP reduction after endurance training of 7 mmHg from SBP and 5 mmHg from DBP was used in the calculation. In order, to provide 80% power to detect a difference of 3 mmHg between the four distinct conditions (exercise intensity and control), a total of 32 patients are indicated to give sufficient power for the study (*n* = 8 for each group). Considering the possible sample loss, 12 patients will be included in each group.

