### Analysis plan

Intragroup and intergroup differences between dependent variables (BP, autonomic modulation, baroreflex sensitivity, blood flow and vascular resistance) considering pre and post interventions (short-term), baseline and post intervention (dependent factor), and exercise intensities or control (independent factor) will be analyzed by two-way analysis of variance (ANOVA) for repeated measures with the Bonferroni post hoc test. Multiple linear regression will be used for analyzing confounding factors (dietary habits and unsupervised physical exercise practice in the follow-up period). Pearson’s correlation test will be used for analyzing the relation between short-term and long-term results. Intention-to-treat will be considered for the patients with an incomplete follow-up period. A *p* value < 0.05 will be considered significant for all evaluations.

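### 80% power for 3 mmHg with 8 patients per group holds for the parallel 8-week comparison only if the SD of the ambulatory BP change is about 2.1 mmHg or less, which is hard to square with the protocol's own mention of high variance

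*Protocol article*

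**What the plan says.** The Power and sample size section sizes the trial on ambulatory monitoring: "Sample size was calculated using ABPM as the main outcome". It opens its reasoning with "Considering the high variance in the results with resistant hypertensive patients" and then states that "BP reduction after endurance training of 7 mmHg from SBP and 5 mmHg from DBP was used in the calculation". The claim itself is "80% power to detect a difference of 3 mmHg between the four distinct conditions (exercise intensity and control), a total of 32 patients", with 8 per group, and 12 per group are enrolled to allow for losses.

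The paragraph gives no SD, correlation, test or sidedness. It does not say whether the 3 mmHg refers to systolic or diastolic pressure, or to the 24-h, awake or sleep mean.

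Two other sections matter. Random allocation sequence describes two designs: an acute phase in which every patient has all four sessions, and an 8-week phase in which patients are randomised to four separate groups. Analysis plan specifies a two-way repeated-measures ANOVA "with the Bonferroni post hoc test", with significance at p < 0.05.

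**The concern.** With 8 patients per group, a 3 mmHg difference between separate groups can be found with 80% power only if patients' BP changes hardly vary. The paragraph points the other way when it invokes high variance. It also names two effect sizes, 7/5 mmHg and 3 mmHg, without saying how they are related, and gives one power figure for a trial with two designs of very different precision.

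This is the only power statement in the article. The Background says it is unclear which exercise characteristics, intensity among them, work better in follow-up studies. A reader told that the trial had 80% power for 3 mmHg could take a non-significant 8-week result as evidence that the intensities do not differ, although the trial might have missed considerably larger differences.

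**Working it through.** **Inputs from the protocol article.** Difference 3 mmHg, power 80%, n = 8 per group (12 enrolled), four groups (Power and sample size); alpha 0.05 and Bonferroni post hoc tests (Analysis plan); parallel groups for 8 weeks (Random allocation sequence).

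**Assumptions.** Two-sided testing; Bonferroni over all 4 × 3 / 2 = 6 pairs, so 0.05/6 = 0.0083 per test; SD of change not stated, so shown as a range.

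**Reproducing the stated figure.** Without an SD, 32 patients cannot be reproduced directly. The check is to find the SD at which the claim is true.

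**Method.** With two time points, the group-by-time test is equivalent to comparing changes between groups. For a pairwise contrast with the error pooled over four groups, df = 4(n − 1) and the noncentrality is λ = d / (SD × √(2/n)). The λ that gives 80% power comes from the noncentral t distribution, and the largest tolerable SD is d / (λ × √(2/n)).

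- n = 8, df = 28, alpha 0.05: λ = 2.902, √(2/8) = 0.5, SD = 3 / (2.902 × 0.5) = **2.07 mmHg**.
- n = 8, alpha 0.05/6: λ = 3.713, SD = 3 / (3.713 × 0.5) = **1.62 mmHg**.
- n = 12, df = 44, alpha 0.05: λ = 2.865, √(2/12) = 0.408, SD = **2.57 mmHg**; with Bonferroni (λ = 3.624), **2.03 mmHg**.
- Overall F test, n = 8, largest gap 3 mmHg: SD limit 1.69 (means 0, 1.5, 1.5, 3), 2.07 (0, 3, 3, 3) or 2.40 (0, 0, 3, 3).
- A one-sided two-sample t test at n = 8 gives 2.29.

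If the SD meant is that of a single BP value, SD of change = raw SD × √(2(1 − r)). A limit of 2.07 then corresponds to a raw SD of 2.07 at a pre-post correlation of 0.5, 2.07/√0.4 = 3.27 at 0.8, and 2.07/√0.2 = 4.63 at 0.9.

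**Power for a 3 mmHg pairwise difference at assumed SDs of change**

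| SD (mmHg) | n = 8, unadjusted | n = 8, Bonferroni | n = 12, unadjusted | n = 12, Bonferroni |
|---|---|---|---|---|
| 4 | 30% | 11% | 44% | 19% |
| 6 | 16% | 4.5% | 22% | 7% |
| 10 | 9% | 2% | 11% | 3% |

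**Difference detectable with 80% power** = λ × SD × √(2/n), for SD 6 to 10:

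- n = 8: 2.902 × 0.5 × SD = 8.7 to 14.5 mmHg (Bonferroni 11.1 to 18.6).
- n = 12: 2.865 × 0.408 × SD = 7.0 to 11.7 mmHg (Bonferroni 8.9 to 14.8).

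**Other readings of the paragraph**

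- 5 or 7 mmHg taken as the SD: power for 3 mmHg at n = 8 is 21% or 13%.
- 7 mmHg taken as the between-group effect: SD limit 4.82 at n = 8 (3.77 with Bonferroni), but this is not the stated 3 mmHg.
- Within-patient comparison of sessions (acute phase): for 80% power at 3 mmHg, the SD of the paired difference may be up to 5.9 with 32 completers and 7.3 with 48, unadjusted.

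**The case against.** The best counter-argument is that the sentence can be read in other ways. If 3 mmHg is the step between successive conditions (means 0, 3, 6, 9), the overall F test at n = 8 tolerates an SD of 5.4. If the 7 mmHg is a fall within a group, a before-after test on 8 patients tolerates 6.1. Both questions suit a trial of graded intensities that plans intragroup and intergroup tests. But each changes the target. The graded pattern spans 9 mmHg and does not give 80% power for a pair of conditions 3 mmHg apart; a fall within one group is not a difference between conditions. The paired reading is sound for the acute phase, but it does not describe 8 patients in each of four training groups.

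Several points on the other side do stand:

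- A condensed article may leave the SD to the full protocol, so its absence is not itself the fault. The fault is a stated power, difference and n that fit together only under a very small SD.
- The mention of high variance refers to cited results and may not mean the SD of an ambulatory change. It makes 2.1 mmHg hard to believe but does not disprove it.
- The SD range of 4 to 10 mmHg is an assumption with no source in the article.
- The 7/5 and 3 mmHg figures are unexplained, but not shown to conflict. One may be a change over time and the other a contrast between conditions.
- The protocol plans no equivalence claim, so the misreading of a null result is a risk, not a stated intention.

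**Conclusion.** The power claim cannot stand as written for the parallel 8-week comparison. It needs an SD of change of about 2.1 mmHg or less at 8 per group (1.6 with Bonferroni over six pairs; 1.7 to 2.4 for the overall F test with a largest gap of 3 mmHg), and about 2.6 for an unadjusted pairwise contrast even if nobody is lost from the 12. Those limits rest only on the stated n, difference, power and alpha, and on two-sided testing. The size of the shortfall depends on an SD that the article does not give.

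A reader might infer that real power is little better than the type I error rate. The figures do not support that in general: at SD 6 unadjusted power is 16% to 22%, three to four times 5%, and the Bonferroni figure of 4.5% at n = 8 should be set against 0.83% per test, about five times lower. Nor does the point extend to the whole trial: the acute crossover may well have adequate power for 3 mmHg.

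**What to change.** Rewrite the Power and sample size paragraph, without enrolling more patients:

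1. Name the ambulatory endpoint (systolic or diastolic; 24-h, awake or sleep), the effect, the assumed SD of change and its basis, the test, and alpha with its sidedness and multiplicity adjustment.
2. Say how the 7/5 mmHg reduction relates to the 3 mmHg difference, and which phase each belongs to.
3. Remove the claim of 80% power for 3 mmHg between parallel groups. Give instead the detectable 8-week difference at 8 and at 12 per group under the assumed SD (the working shows it for SD 6 to 10).
4. State the acute crossover's power separately, with the SD of the within-patient session difference and the number of completers it assumes.
5. Report the 8-week contrasts with confidence intervals, so that a non-significant result is read by what it excludes.

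The cost is one rewritten paragraph, a reporting commitment, and a less favourable figure for the 8-week phase.

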### Analysis plan

Intragroup and intergroup differences between dependent variables (BP, autonomic modulation, baroreflex sensitivity, blood flow and vascular resistance) considering pre and post interventions (short-term), baseline and post intervention (dependent factor), and exercise intensities or control (independent factor) will be analyzed by two-way analysis of variance (ANOVA) for repeated measures with the Bonferroni post hoc test. Multiple linear regression will be used for analyzing confounding factors (dietary habits and unsupervised physical exercise practice in the follow-up period). Pearson’s correlation test will be used for analyzing the relation between short-term and long-term results. Intention-to-treat will be considered for the patients with an incomplete follow-up period. A *p* value < 0.05 will be considered significant for all evaluations.

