**Methods/design:**

This is a randomized controlled clinical trial. Forty-eight patients with resistant hypertension will be submitted to perform four short-term interventions: aerobic exercise sessions (mild-, moderate- and high-intensity) and control session, in random order and on separate days. After the short-term sessions, the patients will be randomly allocated into four groups for 8 weeks of follow-up: mild-, moderate- and high-intensity aerobic exercise, and a control group. The primary outcome is the occurrence of blood pressure reduction (office and ambulatory analysis, and acute and chronic effects). Secondary outcomes are autonomic and hemodynamic mechanisms: cardiac and vasomotor autonomic modulation, spontaneous baroreflex sensitivity, forearm blood flow and vascular resistance.

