### Random allocation sequence

Randomization will be done using a sealed opaque envelope. All the patients will be submitted to perform four short-term interventions (within design): mild aerobic exercise, moderate aerobic exercise and high-intensity aerobic exercise and a control session, in random order and on separate days. After the short-term sessions, all the patients will be randomly allocated into four groups and followed up for 8 weeks (between design): mild aerobic exercise group, moderate aerobic exercise group, high-intensity aerobic exercise group and the control group.

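### The analysis plan gives both phases one ANOVA with intensity as an independent factor, which contradicts the acute phase, where every patient does all four sessions.

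*Protocol article*

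**What the plan says.** Under Random allocation sequence the article separates two designs. In the acute phase, "All the patients will be submitted to perform four short-term interventions (within design"), and these take place "in random order and on separate days". For training, "all the patients will be randomly allocated into four groups and followed up for 8 weeks (between design"). The abstract gives the number in the acute phase: "Forty-eight patients with resistant hypertension will be submitted to perform four short-term interventions".

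The Analysis plan then states a single model for both phases. Time is the repeated element, "considering pre and post interventions (short-term), baseline and post intervention (dependent factor"), and intensity or control is the other: "exercise intensities or control (independent factor) will be analyzed by two-way analysis of variance (ANOVA) for repeated measures", followed by Bonferroni post hoc tests. The significance rule is that a p "value < 0.05 will be considered significant for all evaluations".

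The acute effect belongs to the primary outcome. The abstract includes both acute and chronic blood pressure effects in it.

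**The concern.** In that sentence one factor is called dependent and the other independent. Independent cannot simply mean explanatory, because time is explanatory too and carries the opposite label, and because the outcomes are named separately as dependent variables. The natural reading is repeated versus between-patient. That is right for the 8-week groups and wrong for the acute sessions.

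Two things are at stake in the acute phase. Each patient serves as their own control, and a between-patient treatment of intensity throws that pairing away in the comparisons the trial most wants to make: whether intensities differ, and whether each differs from seated rest. The same model also counts 48 patients as 192 when it averages the pre-post change over all sessions, which makes that average look more certain than it is. The sentence covers the autonomic and vascular outcomes as well as blood pressure.

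**Working it through.** **Inputs from the article.** 48 patients, 4 sessions each, so 48 × 4 = 192 session records; alpha 0.05 (taken as two-sided). For the power illustration, the 3 mmHg in Power and sample size: "to provide 80% power to detect a difference of 3 mmHg between the four distinct conditions".

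**Inputs not in the article (assumptions).** SD of a session's change, s, taken as 6 or 8 mmHg. Correlation of a patient's changes across sessions, rho, taken as 0.3 to 0.7, with 0 and 0.1 for comparison. The stated sample size of 32 can be neither reproduced nor refuted, because no SD or correlation is reported with it. Nothing below depends on it.

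**Reduction.** With one pre and one post value per session, the time-by-intensity test equals an ANOVA on the changes (post minus pre). Give each change variance s² and each pair of changes within a patient correlation rho.

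*Contrast of two sessions.*
- Literal (between-patient) variance: 2s²/48
- True variance: 2s²(1 − rho)/48
- Stated SE ÷ true SE = 1/√(1 − rho)

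*Pre-post effect pooled over the four sessions.*
- Literal variance: s²/192
- True variance: s²(1 + 3rho)/192
- True SE ÷ stated SE = √(1 + 3rho)
- Actual type I error ≈ 2[1 − Φ(1.96/√(1 + 3rho))]

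| rho | Contrast SE too large by | Pooled SE too small by | Type I error, pooled effect |
|---|---|---|---|
| 0 | 1.00 | 1.00 | 5% |
| 0.1 | 1/√0.9 = 1.05 | √1.3 = 1.14 | 9% |
| 0.3 | 1/√0.7 = 1.20 | √1.9 = 1.38 | 16% |
| 0.5 | 1/√0.5 = 1.41 | √2.5 = 1.58 | 22% |
| 0.7 | 1/√0.3 = 1.83 | √3.1 = 1.76 | 27% |

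These columns do not depend on s. Simulation (20,000 runs per cell) agrees, with pooled type I error of 15% to 16% at rho 0.3, 22% at 0.5 and 27% at 0.7.

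**Which tests go wrong, and which way.** In the same simulations, the literal model's exercise-versus-control contrast has a true type I error of about 2% at rho 0.3, 0.6% at 0.5 and below 0.1% at 0.7. It is conservative. The pre-post test of any single session stays at about 5%. Only the pooled pre-post effect is anti-conservative.

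**Power of the intensity test** if all three exercise sessions lower blood pressure by 3 mmHg more than control:

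| rho | s = 6: literal / within-patient | s = 8: literal / within-patient |
|---|---|---|
| 0.1 | 70% / 75% | 41% / 47% |
| 0.3 | 69% / 86% | 37% / 59% |
| 0.5 | 69% / 96% | 31% / 76% |
| 0.7 | 69% / 100% | 23% / 94% |

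The direction is the same throughout; the size of the loss depends on s and rho.

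**Session order.** With an assumed drift of 2 mmHg per session position, rho 0.5 and s = 6, a within-patient model without an order term still estimates a true −3 mmHg as −3.00. Its SE rises from 0.86 to 1.01 mmHg and its power falls from 95% to 86%. Random order protects against bias, so only precision is lost.

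**The case against.** The strongest reply is that the wrong model is inferred. The article nowhere says that 48 patients will be analysed as 192. A two-way repeated-measures ANOVA can have both factors within patient, and the authors plainly know the two designs differ because they label them. On this view the sentence is a compressed description in a journal article. Part of this stands: the analysts may intend the correct model. But the sentence does more than leave a detail open. It assigns a role to each factor and names the short-term data in doing so, and that role conflicts with the acute design.

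A reader might infer that the plan would produce false claims about exercise intensity. It would not. The type I inflation is confined to an average over three exercise sessions and the seated control, which is not what the Research question asks. Contrasts between sessions err on the safe side, and single-session pre-post tests hold their level.

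A reader might also infer a collapse in power. That rests on assumption: with s = 6 the literal model keeps about 69% to 70% at every rho shown. The correlation is between changes, from which a patient's stable level has already been subtracted, so values below 0.3 are plausible and the loss would then be small.

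Finally, the lack of a session-order term might be read as a bias. Order is randomised, so it is not one, and such a term is commonly left to a fuller analysis plan.

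**Conclusion.** The point holds as a contradiction between the Analysis plan and the acute design set out under Random allocation sequence, affecting the acute part of the primary outcome and the secondary outcomes measured with it. If the text is followed literally and rho lies between 0.3 and 0.7, contrasts between sessions carry standard errors 1.20 to 1.83 times too large, and the pooled pre-post effect carries one 1.38 to 1.76 times too small, with a type I error of about 15% to 27%. The main practical cost is lost power for comparing sessions, in an amount that cannot be fixed without an SD. The ratios rest on equal variances and a common correlation across sessions, and shrink to 1 at rho = 0. The documents do not establish that the wrong model will be run, only that it is the one the wording describes.

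**What to change.** Replace the single sentence with two.

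- **Acute phase:** intensity/control and time are both within-patient factors, in a two-within-factor repeated-measures ANOVA or, equivalently, a mixed model with patient as random effect. Each exercise session is contrasted with the same patient's control session.
- **8-week phase:** group is the between-patient factor and time the repeated factor, as the present wording already implies.

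A term for session position (1 to 4) in the acute model is optional and serves precision only. The change costs wording: no extra patients, visits or measurements. The article reports recruitment as still open, so it can be settled before analysis.

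### The Bonferroni post hoc test is valid, but Holm's step-down version keeps the same 5% family-wise error and is somewhat more powerful

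*Protocol article*

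**What the plan says.** The protocol article, under Statistical analysis, Analysis plan, prescribes "two-way analysis of variance (ANOVA) for repeated measures with the Bonferroni post hoc test". The test applies to "Intragroup and intergroup differences between dependent variables", so it covers contrasts over time within a group as well as contrasts between conditions. The significance rule is a p "value < 0.05 will be considered significant for all evaluations". No step-down version is named, and neither the family nor the number of comparisons is stated.

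Under Random allocation sequence, the 8-week phase has four parallel groups: "mild aerobic exercise group, moderate aerobic exercise group, high-intensity aerobic exercise group and the control group". In the short-term phase every patient undergoes all four conditions.

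Under Power and sample size, the target is "80% power to detect a difference of 3 mmHg between the four distinct conditions", with 8 patients per group, raised to 12 for losses. The section also states that "BP reduction after endurance training of 7 mmHg from SBP and 5 mmHg from DBP was used in the calculation". It speaks of high variance in this population but gives no SD.

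**The concern.** Four conditions form six pairs. In its usual single-step form, Bonferroni judges every pair at 0.05/6, even after some pairs have already been shown to differ and fewer true null hypotheses can remain. Step-down methods use that information. They control the same error rate and can only add rejections. In a trial with 12 patients per arm, where the conditions are to be compared with one another, some true differences may go undeclared because of the post hoc test alone.

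**Working it through.** **Inputs.** Four conditions and 12 per group come from the protocol, as do the 7 mmHg and 3 mmHg effects and the 0.05 level (taken as two-sided). The SD of change is assumed, because none is given: 6, 8 and 10 mmHg, with 2 mmHg as a favourable extreme. The six pairs are derived: 4 × 3 / 2 = 6.

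**The plan's own figure.** The 8 per group cannot be reproduced without an SD. Solving n = 2(1.96 + 0.84)² SD² / 3² for n = 8 gives an SD of about 2.14 mmHg (normal approximation, no multiplicity adjustment). Nothing below depends on this figure.

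**Thresholds for the ordered p values, six pairs.**

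| Step | 1 | 2 | 3 | 4 | 5 | 6 |
|---|---|---|---|---|---|---|
| Bonferroni | 0.0083 | 0.0083 | 0.0083 | 0.0083 | 0.0083 | 0.0083 |
| Holm (0.05/6, /5, /4, /3, /2, /1) | 0.0083 | 0.0100 | 0.0125 | 0.0167 | 0.0250 | 0.0500 |
| Shaffer (0.05/6, /3, /3, /3, /2, /1) | 0.0083 | 0.0167 | 0.0167 | 0.0167 | 0.0250 | 0.0500 |

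Shaffer's divisors follow from logic. Among four means the number of true equalities can only be 6, 3, 2, 1 or 0, so after one rejection at most three remain. Both step-down rows are never stricter than Bonferroni, so they reject whatever it rejects.

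**Power, 12 per arm, control 7 mmHg from three equal exercise arms** (40,000 simulated trials per setting, pooled variance, 44 df). Average power per true pair:

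| SD (assumed) | Bonferroni | Holm | Shaffer |
|---|---|---|---|
| 6 | 54% | 57% | 61% |
| 8 | 28% | 30% | 33% |
| 10 | 16% | 17% | 19% |

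The Bonferroni column can be checked directly. At SD 6 the noncentrality is 7 / (6 × √(2/12)) = 2.86, the critical t at 0.05/6 two-sided is 2.76, and the power is 54%.

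**Other settings, same arm size.**
- Control 3 mmHg from three equal exercise arms, SD 6/8/10: power per pair is about 7/4/3% with Bonferroni. Holm adds about 0.1 to 0.4 points and Shaffer about 0.5 to 1.3.
- Four different means (0, 3, 5, 7 mmHg), SD 2: Bonferroni 76%, Holm 86%. This is the largest gain seen. At SD 5 it is 26% to 28%, and at SD 8 it is 9% to 10%.
- At least one true difference found (7 mmHg; Bonferroni, then Shaffer): 77.4 and 77.4% at SD 6, 49.4 and 49.5% at SD 8, 32.0 and 32.1% at SD 10.
- All three exercise-versus-control differences found (7 mmHg, SD 6): 30% Bonferroni, 36% Holm, 41% Shaffer.

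**Family-wise error.** With all four arms equal it is about 4% for all three methods. The worst partial null is two well-separated pairs of equal means. There the last two step-down thresholds are 0.025 and 0.05, and the error is close to 1 − 0.975² = 4.9%; simulation of Shaffer's version gave 4.9 to 5.0%. It stays within 5%.

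**The case against.** The case for leaving the text alone is fair. Bonferroni is a recognised, prespecified method that controls the family-wise error and comes with matching simultaneous intervals. Nothing in the protocol is contradicted. That stands, and it sets the rank of the point.

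A reader might also infer more than the documents and the arithmetic support:

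- *That precision is lost.* Estimates and standard errors are the same under either method. Only the number of declared differences changes.
- *That the exercise intensities would be separated better.* In the 7 mmHg scenario the three exercise arms are equal, so the whole gain lies in exercise-versus-control pairs. A gain between intensities appears only if the four means differ, and it is large only if the SD is very small.
- *That the change is worth about 13% more patients.* Bonferroni with about 13.5 per arm matches Shaffer with 12 (13.5/12 = 1.125). This holds only for average power per pair, for Shaffer rather than Holm, and in the 7 mmHg scenario. The first rejection becomes no easier.
- *That Shaffer's divisors can simply replace Bonferroni.* The Analysis plan also covers intragroup differences. The sequence 6, 3, 3, 3, 2, 1 is valid only for all pairs of one set of four means. An outright swap would leave the within-group and time contrasts with no named adjustment. Holm works for a family of any size.
- *That these figures describe the short-term phase.* There all patients undergo all four sessions, so 12 per arm does not apply. That phase was not simulated. Holm's error control holds there under any dependence, but the size of the gain is unknown.

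**Conclusion.** The point holds as an optional gain in efficiency. At the same 5% family-wise error, Holm is never less powerful than single-step Bonferroni and on average finds more true differences. In the 8-week phase with 12 per arm, Holm's gain is about 1 to 3 points of power per true pair at 7 mmHg with SD 6 to 10. It is a few tenths of a point at 3 mmHg, and about 10 points in the most favourable setting examined (four different means, SD 2). It does not repair low power.

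The figures rest on assumed SDs, a two-sided 0.05, equal variances, full retention of 12 per arm, a family of six between-condition pairs, and the usual single-step reading of the Bonferroni wording. The direction of the result does not depend on the SDs or on the family size. Neither method controls error across the several blood pressure measures.

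**What to change.** In the Analysis plan, keep the repeated-measures ANOVA and name Holm's step-down Bonferroni adjustment as the post hoc method, applied to the same set of intragroup and intergroup comparisons in both phases. If Shaffer's procedure is wanted for more power, restrict it to families that consist of exactly the six pairs of four condition means, and keep Holm for the intragroup and time contrasts.

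The cost is a change of wording, with no extra patients or data; it should be made before the outcome data are analysed. The downside is that step-down tests have no simple matching simultaneous intervals. Bonferroni intervals can still be displayed, with a note that such an interval may include zero for a pair that the step-down test rejects.
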